#### Secondary

1. Effectiveness of PRF treatment of DRG, when compared to placebo, as a treatment in patients with CLR: outcome measured as decrease in VAS scores (0 to 10) from baseline measured at recruitment. For definition of success we would consider at least 50% decrease in VAS scores assessed at 4 weeks.

2. Assessment of short-term side effects: percentage of patients having side effects after PRF treatment assessed at 1 week, compared with the placebo group. Assessment of persisting side effects: percentage of patients having side effects after PRF treatment, beyond 1 week, compared with placebo group. Short-term side effects (within 1 week – recorded at the first visit):

Nausea

Headache

Transient increase in pain

Fever (temperature in°C)

Transient paresis/paraesthesia

Dysesthesia

Long-term side effects (persisting side effects assessed at visits 1 week and at 6 weeks):

Infection at the site

Meningitis

Epidural abscess

Hyposensibility

Paralysis/paresis

Dysesthesiae

Any other

3. Improvement in ODI: success defined as at least 50% improvement (or decrease) in ODI measured at 4 weeks, compared with placebo group.

4. Decrease in the analgesic medications used: percentage of patients with increase or decrease in their medication use (either in dose, frequency), compared with placebo group.

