### Trial design, outline, and flow chart

#### Sample size, recruitment rate

Sample size has been determined based on feasibility considerations. Total duration of recruitment planned is 8 (clinically active) months. The proposed target is recruitment for 8 months, with an expectation of at least four patients every month, with a total of 32 patients for the study. Potential to recruit patients, as four patients every month has been calculated based on the transforaminal steroid injections (TFESI) performed in the last 3 to 6 months and booked for the next 3 to 6 months (calculated as monthly) at St Joseph’s Healthcare; data obtained from St Joseph’s Healthcare, Department of Anesthesia and Pain. TFESI represents a well-accepted, presently performed intervention for patients of CLR and most patients suitable for that are potential recruits for this study.

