#### Randomization

Patients will be randomly allocated to each group using a 1:1 ratio. The allocation will be done in blocks using block sizes of 2, 4, and 6.

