## Discussion

The results of this pilot study would primarily give us information about the patient recruitment and study methodology. This is being done as there are no previous studies (RCTs) to indicate the successful effects of PRF in CLR. The initial study proposal was to conduct an RCT comparing PRF-DRG with TFESI, which have proven to be more successful than midline ESIs for lumbar radiculopathy [52], and are probably the most effective intervention available. However our literature search showed that so far, there were no RCTs involving sufficient participant numbers to evaluate the efficacy of PRF. The only RCT by Van Zundert *et al.*[16] on cervical radicular pain had only 19 participants in either group. Keeping this in mind we devised this proof of concept study to evaluate the efficacy of PRF as compared to placebo.

It is very challenging to devise and conduct a placebo controlled trial in interventional pain medicine. Because of the nature of the problem, which involves significant suffering for a long time, patients may be unwilling to participate as blind participants. CLR patients would have had a trial of most medications and simple interventions before they go on to have complex spinal interventions, such as PRF-DRG. It may also be difficult to have such patients to be under long periods of follow-up after a blind intervention, especially if it is not of benefit to the patient. This trial would be able to tell us whether we were able to recruit patients as expected for the trial and also whether they continue to be participants of the study for the whole duration. The other important and novel aspect of this study which merits attention is the technique of patient blinding during the procedure. Although we will not be formally evaluating the blinding process, it will be interesting to know if we faced significant challenges and if such a methodology needs to be appropriately modified for a future trial. The study would also assess the outcomes of pain relief from PRF compared to placebo. Apart from telling us if PRF is successful, the study would also indicate the difference in pain relief in terms of absolute reduction in VAS scores. This is necessary to assess the number of study participants for a future trial. The assessment of side effects is included to understand if there are major or minor side effects and risks which need to be better studied and informed to the patients.

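### Success in pain and disability is defined by a 50% cut; at about 16 per arm the baseline-adjusted mean difference should be the main efficacy summary, with responder rates as support

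*Protocol article*

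**What the plan says.** Under Primary and secondary outcome measures, Secondary, item 1 names a continuous pain measure first: "outcome measured as decrease in VAS scores (0 to 10) from baseline measured at recruitment". The next sentence adds the success criterion: "For definition of success we would consider at least 50% decrease in VAS scores assessed at 4 weeks". Item 3 states ODI only as a cut against placebo: "success defined as at least 50% improvement (or decrease) in ODI measured at 4 weeks".

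Elsewhere in the protocol article:

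- Secondary research questions ask about a fall in VAS at 4 weeks, and about any ODI improvement at 4 weeks, 2 months and 3 months.
- Duration of treatment and follow-up collects VAS and ODI as scores at 1 week, 4 weeks, 2 months and 3 months. A baseline ODI is also taken.
- The Discussion says "the study would also indicate the difference in pain relief in terms of absolute reduction in VAS scores", and gives sizing the future trial as the reason.
- Statistical tests describes participants and feasibility outcomes. It names no efficacy test.
- On size: "Sample size has been determined based on feasibility considerations".

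**The concern.** The protocol has scores at baseline and at 4 weeks in both arms, but the word success is attached to a yes/no version of them. A patient with a 49% fall and one with a 51% fall count as opposite results, while falls of 51% and 95% count as the same.

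What a pilot can usefully pass on about efficacy is a mean difference, its confidence interval and an SD. A responder percentage supplies neither the mean difference nor the SD. If the cut becomes the headline, the VAS result will be reported less precisely than the data allow. For ODI, the stated outcome would give no continuous estimate at all, although the research question asks about any improvement.

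**Working it through.** **Inputs from the protocol article.** Recruitment: "Total duration of recruitment planned is 8 (clinically active) months", "with an expectation of at least four patients every month, with a total of 32 patients for the study". So 4 × 8 = 32, which reproduces the stated total. Allocation: "Patients will be randomly allocated to each group using a 1:1 ratio", so 32 / 2 = 16 per arm. Entry requires VAS of at least 6 out of 10.

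**Assumed, because the document gives no figure.** Two-sided 5% level; 4-week VAS SD 2 to 2.5; correlation r between baseline and 4-week score 0.2 to 0.5; response rates 20 to 50%; true difference 1.5 to 2.5 points.

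**Step 1: information kept by a cut.** For a normal score cut so that a proportion p responds, efficiency relative to a baseline-adjusted mean is φ(z_p)² / [p(1−p)] × (1−r²).

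- p = 0.5: 0.637 × 0.96 = 0.61 at r = 0.2; 0.637 × 0.75 = 0.48 at r = 0.5.
- p = 0.3: 0.576 × 0.96 = 0.55; 0.576 × 0.75 = 0.43.
- p = 0.2: 0.490 × 0.96 = 0.47; 0.490 × 0.75 = 0.37.

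The loss is therefore 39% to 63%, equivalent to needing 1/0.61 = 1.6 to 1/0.37 = 2.7 times as many patients.

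**Step 2: confidence interval half-widths at 16 per arm.**

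- Responder difference, 30% v 50%: 1.96 × √[(0.3×0.7 + 0.5×0.5)/16] = 0.33. With 50% in both arms: 1.96 × √[2×0.25/16] = 0.35.
- Adjusted mean difference, 2.045 × SD × √(1−r²) × √(2/16): SD 2, r = 0.5 gives 1.25; SD 2.5, r = 0.3 gives 1.72; SD 2.5, r = 0.2 gives 1.77. Simulated values for r of 0.3 to 0.5 run from 1.22 to 1.65.

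**Step 3: simulated power.** 4,000 runs per scenario, baseline mean about 7.5 held within 6 to 10, placebo 4-week mean 5.5, true difference 2 points.

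| SD | r | Response rates, placebo v PRF | Fisher | Chi-square | Change-score t | Baseline-adjusted |
|---|---|---|---|---|---|---|
| 2 | 0.3 | 18% v 56% | 45% | 64% | 80% | 80% |
| 2 | 0.5 | 17% v 56% | 50% | 67% | 88% | 87% |
| 2.5 | 0.3 | 24% v 55% | 29% | 44% | 62% | 61% |
| 2.5 | 0.5 | 23% v 55% | 32% | 48% | 71% | 69% |

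Over these and the matching runs at 1.5 and 2.5 points, the adjusted analysis gains about 11 to 21 percentage points over chi-square.

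**Step 4: a common scale.** Percentage points and VAS points cannot be compared directly, so divide each standard error by its effect. For SD 2, r = 0.3:

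- Responders: √[(0.18×0.82 + 0.56×0.44)/16] = 0.157; 0.157/0.38 = 0.41.
- Mean difference: simulated half-width 1.36, and 1.36/2.045 = 0.665; 0.665/2 = 0.33.
- Efficiency (0.33/0.41)² ≈ 0.65, a loss of about 35%.

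This is just under the range in step 1. A percentage cut is taken against the patient's own baseline, so it already uses some of the baseline information that the formula credits to the adjusted model alone.

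**Step 5: where the gain comes from.** The change-score and adjusted columns differ by no more than about 2 points. The simulation took a baseline SD of about 1.05, so the regression slope r × SD / 1.05 runs from 0.3×2/1.05 = 0.57 to 0.5×2.5/1.05 = 1.19. A plain change score assumes a slope of 1, so it is already near the best choice. The gain is from not dichotomising.

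**The case against.** A reader might infer that VAS efficacy is judged by the cut alone, and that the Discussion contradicts the outcome section. Neither holds. Item 1 names the decrease in VAS before it gives the success threshold, and the absolute reduction in the Discussion is that same measure. Reporting a mean change and a responder rate together is ordinary practice.

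A reader might also infer that the cut throws away most of the information. That depends on unknowns. The loss passes half at a 20% response rate, or at r near 0.5, but is about 39 to 48% at response rates of 30 to 50% with r of 0.2 to 0.3. Setting Fisher's test against the adjusted model exaggerates the gap, because the document names no test and Fisher is conservative at this size. If the effect were as large as in the cervical sham trial that the protocol tabulates (82% v 25 to 33%), 16 per arm would give a responder comparison 83 to 94% power.

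Nor is any stated power wrong. This is a feasibility pilot, its progression criteria concern recruitment, and no efficacy test is promised. The exact model may well stand in an analysis plan not shown, so its absence is no fault.

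These objections limit the point for VAS. They do not answer it for ODI, where the cut is the only measure stated. They also leave a dichotomy as the definition of success in a trial whose efficacy output is needed as an estimate.

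**Conclusion.** The point holds in limited form. The protocol fixes 4-week success as a 50% cut in VAS and in ODI. For ODI nothing else is specified; for VAS a continuous measure stands beside it. A responder comparison at about 16 per arm is clearly less precise than one on the scores. The loss is roughly 40 to 60% by formula, with the lower end (or slightly less) more realistic for a percentage cut. The responder half-width of about 33 to 35 percentage points is as large as the responder difference of 31 to 39 points that a true 2-point VAS benefit produced in the simulations. The mean-difference half-width of about 1.2 to 1.7 points is smaller than that benefit.

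All these sizes rest on an assumed SD, correlation, response rate and effect. The direction does not: the continuous analysis was more precise in every scenario tried. No ODI figures were available, so for ODI only the general formula applies. The documents do not support reading this as a power error, as an internal contradiction over VAS, or as a fault in leaving out covariance adjustment.

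**What to change.** State the main efficacy summary as the PRF-minus-placebo difference in 4-week VAS, with its 95% CI and the SD, from a linear model adjusted for baseline VAS. Define ODI at 4 weeks in the same way, adjusted for baseline ODI. Keep the percentages reaching a 50% reduction in each score as supportive description.

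A repeated-measures model over 1 week, 4 weeks, 2 months and 3 months is optional; it would also serve the ODI research question about the later visits.

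The cost is analysis wording only. Every score is already collected, and the Trial status section shows recruitment still open, so the change can be recorded before outcomes are compared by group.

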### Duration of treatment and follow-up

Duration of treatment period will involve approximately 30 to 60 min of actual intervention done in the OR. The duration of complete follow-up will be for 3 months after the intervention with the following interval follow-up assessments: (1) 30 min post-procedure in recovery, (2) 24 h after - by a phone call (only VAS and side effects); (3) at 1 week post-procedure visit to the assessor (VAS, ODI, medications, side effects); (4) at 4 weeks post-procedure visit to the observer for assessment for success (VAS, ODI, medications, side effects); (5) at 2 months post-procedure-visit to observer (VAS, ODI, medications, side effects); (6) at 3 months post-procedure visit to the observer - last follow-up visit (VAS, ODI, medications, side effects).

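### Short-term and persisting side effects are defined by time but filled from lists split by type of event, so the classification of some first-week events is not fixed

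*Protocol article*

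**What the plan says.** All of the following is in the protocol article.

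**Definitions** (Primary and secondary outcome measures, Secondary, item 2). The short-term outcome is the "percentage of patients having side effects after PRF treatment assessed at 1 week, compared with the placebo group". The second outcome is "Assessment of persisting side effects: percentage of patients having side effects after PRF treatment, beyond 1 week, compared with placebo group". Both are defined by time, and neither sentence limits the type of event.

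**Lists** (same item).
- The first is headed "Short-term side effects (within 1 week – recorded at the first visit" and has six items: nausea, headache, increased pain, fever, paresis or paraesthesia, and dysesthesia. Paresis or paraesthesia counts as transient only, and the pain item reads "Transient increase in pain". There is no catch-all.
- The second is headed "Long-term side effects (persisting side effects assessed at visits 1 week and at 6 weeks" and has seven items: site infection, meningitis, epidural abscess, hyposensibility, paralysis or paresis, dysesthesiae, and a closing *any other*.

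**Collection** (Duration of treatment and follow-up). Side effects are collected at a 24 h call and at four visits, from "at 1 week post-procedure visit to the assessor (VAS, ODI, medications, side effects" to "at 3 months post-procedure visit to the observer - last follow-up visit (VAS, ODI, medications, side effects". No list is attached to these contacts. Under Methodology and techniques, a blinded observer also checks for side effects before discharge.

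**Purpose** (Discussion). Side effects are assessed "to understand if there are major or minor side effects and risks which need to be better studied and informed to the patients".

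**The concern.** A percentage defined by time should be filled by asking about the same events in each window and then sorting them by date. Here membership of a list does part of the sorting. An event in the first week counts as short-term without difficulty only if it is one of six named types, although the definition speaks of side effects in general. Two careful readers could place the same patient in different percentages, or one of them in none.

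Side effects are a stated secondary objective, and the results are meant to inform what patients are told. In a trial of 32 patients, a few ambiguous cases can change the reported rates visibly, so the rule should not be chosen after the allocation is known.

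**Working it through.** The protocol gives no figure to reproduce. The check compares the lists with the definitions and then sizes one ambiguous patient.

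**1. Overlap of the lists.** Short-term items: 6. Long-term items: 7. Common to both: 2 (dysesthesia; paresis, which on the short-term list must be transient).
- On the short-term list only: 6 − 2 = 4 (nausea, headache, increased pain, fever).
- On the long-term list only: 7 − 2 = 5 (site infection, meningitis, epidural abscess, hyposensibility, *any other*).

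**2. Cases, following the lists literally.** The first visit is taken to be the 1-week visit, since the 24 h contact is a telephone call.

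| Case | Short-term percentage | Persisting percentage |
|---|---|---|
| Nausea on day 1, resolved | Counted: named item | Not counted: not beyond 1 week |
| Hyposensibility, or an event on neither list, resolved before the 1-week visit | No item and no catch-all | Not beyond 1 week |
| Site infection or hyposensibility present at the 1-week visit | No item | Recordable, but labelled long-term before it is known to last beyond 1 week |
| Increased pain still present at the 1-week visit | Item requires transience, which cannot yet be judged | Recordable under *any other*, with the same labelling problem |
| Headache, increased pain or fever at 4 weeks or later | Not applicable | Counted under *any other* |
| Meningitis or epidural abscess present at the 1-week visit | No item | Recordable by name |

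The second row enters neither percentage. Rows three, four and six are recorded, but which percentage they belong to depends on the reader. Row five is not a problem.

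The second row is not far-fetched. Table 3 reports a patient with a small area of low sensation after this procedure, so the authors know the event, and both arms receive lidocaine before treatment. How often it would occur and resolve within a week is not given.

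**3. Size of one case.** Planned total 32, allocation 1:1, so 32 / 2 = 16 per arm. One patient: 1 / 16 = 6.25 percentage points. For k patients in one arm the shift is k × 6.25:
- k = 1: 6.25 points
- k = 2: 12.5 points
- k = 3: 18.75 points

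The documents give no basis for predicting k. If both arms have the same k, both rates shift but their difference does not. If the numbers differ by one patient, the difference between arms shifts by 6.25 points.

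**4. Direction.** Leaving an event out lowers the short-term rate. Labelling a first-week event long-term lowers the short-term rate and may raise the persisting one. The two percentages need not move the same way.

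**The case against.** The strongest reply is that the lists only illustrate. Both outcome sentences speak of patients having side effects without naming types, the follow-up schedule collects side effects without restriction, and nothing says that only listed events count. The long-term list, with its catch-all, is also in use at the 1-week visit. On that reading a serious event present at 1 week is recorded, and later headache, pain or fever has a home.

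Most of this stands, and it rules out two stronger readings. A reader might infer that events off their assigned list have no place to be counted at all. The documents do not support that: *any other* takes persisting events, and the long-term list applies at 1 week. A reader might also infer that both percentages are understated in both arms. That would need the lists to be closed and the catch-all to be ignored, and it is not shown.

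The reply does not settle the short-term percentage. An open reading needs a rule that assigns a first-week event such as hyposensibility to the short-term outcome, and the text instead places it under a long-term heading. An event resolved by 1 week gets no help from the catch-all, because it does not meet the persisting definition.

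It can also be said that this is detail for the case report form, which an article may leave out. But the article prints both definitions and both lists, and the fault lies in what they fix together, not in something omitted.

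**Conclusion.** The point holds as a classification defect, mainly of the short-term percentage. The definitions sort by time and the lists sort by type; the short-term list has no catch-all and requires transience for two items; and the 1-week visit serves both lists although persisting means beyond 1 week. Under a literal reading, a first-week event off the short-term list is omitted from the short-term rate or labelled long-term, and if resolved by 1 week it enters neither rate.

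The size is 6.25 percentage points of an arm's rate per affected patient. This assumes that 32 patients are enrolled, that the split is 16 and 16, and that the lists are applied as printed. The number of affected patients is unknown, so no overall bias is claimed. In a small feasibility trial this is worth correcting, but it does not threaten the primary outcomes.

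Two other inconsistencies in the same outcome are separate and lend this point no weight: the 6-week assessment is not in the follow-up schedule, and the secondary research question places short-term at 4 weeks and long-term beyond 3 months.

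**What to change.** 1. At every remaining scheduled contact, use one checklist holding all items of both lists plus *any other*, with increase in pain not limited to transient episodes. Record onset and resolution dates.
2. Before unblinded analysis, write down a rule that classifies every recorded event as short-term or persisting by those dates, or by the visit at which it was recorded where dates are missing. The list on which an event stands should play no part. An event that starts in the first week and continues beyond it should count in both percentages, and the rule should say so.
3. State the single time boundary that the rule uses, since the outcome section and the research question differ on it.

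The cost is a form and wording change and slightly longer contacts, with no new visits. The limit is timing. The Trial status section reports interventions completed in 28 of 32 patients, leaving 32 − 28 = 4. For patients already past their first week, the change can only reclassify what was recorded; an event that was never asked about cannot be recovered. The report should say so.

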### Secondary research questions

1. Is pulsed radiofrequency of DRG effective for pain relief - measured as a decrease in VAS, measured at 4 weeks?

2. Is application of PRF associated with any short-term (at 4 weeks) or long-term persisting (beyond 3 months) side effects?

3. Is there any improvement in Oswestry Disability Index (ODI) in patients of CLR after PRF; measured at 4 weeks, 2 months, and 3 months?

4. Is there any decrease in analgesic (medications) use in patients with CLR after application of PRF; measured at 1 week, 4 weeks, 2 months, and 3 months?

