
Target location: the DRG, which is an enlargement formed by the dorsal nerve root just proximal to its junction with the spinal nerve, lies within the dural sleeve and occupies the upper, medial part of the intervertebral foramen [46]. It is confirmed with an anteroposterior fluoroscopy view in which it is advanced, if required, until the tip is located one-third to halfway into the pedicle column.

Target confirmation [46]: appropriate fluoroscopic placement of needle near DRG at the lumbar area is noted; on anteroposterior X-ray projection, the DRG is described to lie immediately behind the lateral aspect of the facet column at all spinal levels and on lateral X-ray projection, it is localized to the dorsocranial quadrant of the intervertebral foramen (IVF). Proximity of the needle to the DRG is determined by appropriate sensory stimulation with 50 Hz, at more than 0.4 V (avoids intra-ganglionic placement), and less than or equal to 0.6 V; motor stimulation at 2 Hz with threshold 1.5-2 times greater than sensory threshold to avoid placement near the anterior nerve root. A radiculogram done also confirms the appropriate placement and helps recognize intradural placement of the needle. Both the groups will have their respective DRG stimulated for sensory confirmation. Only lidocaine 1% 0.5 mL shall be given in both groups before carrying out the treatment.

Treatment: once positioned the physician shall indicate to the RF technician as ‘treatment’ only, at which time either PRF or placebo (only continuing sensory stimulation at a low frequency of 0.2 V is applied) without revealing. Application of intervention: in Group A, PRF; PRF would be applied for 120 s at 42°C. Group B, placebo; the needle would be continuously stimulated at a low voltage to give a sensation of PRF application and also to obtain the necessary noise to blind the patients. In both groups the same procedure is done at all the involved spinal segmental levels. After the procedure the patient is shifted to recovery area to be monitored, observed and managed for any side effects. The observer, blind to the interventions, will record the pain scores and also check for side effects observed before the patient is discharged home.

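### The short-term side-effect outcome rests on the 1-week visit alone and can miss early events that the recovery check and 24 h call already record

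*Protocol article*

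**What the plan says.** The outcome is in Primary and secondary outcome measures, Secondary, item 2. The short-term measure is the "percentage of patients having side effects after PRF treatment assessed at 1 week, compared with the placebo group". The event list below it is headed "Short-term side effects (within 1 week – recorded at the first visit" and has six entries: nausea, headache, "Transient increase in pain", fever (as a temperature in °C), "Transient paresis/paraesthesia" and dysesthesia.

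Three contacts up to 1 week collect side effects:

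- **Recovery.** Methodology and techniques (treatment paragraph) says that the blinded observer "will record the pain scores and also check for side effects observed before the patient is discharged home". Duration of treatment and follow-up puts this assessment at 30 min.
- **24 h.** Duration of treatment and follow-up lists a contact "24 h after - by a phone call (only VAS and side effects".
- **1 week.** The same section lists the next contact "at 1 week post-procedure visit to the assessor (VAS, ODI, medications, side effects".

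Secondary research questions, item 2, frames the same outcome with other windows: "Is application of PRF associated with any short-term (at 4 weeks) or long-term persisting (beyond 3 months) side effects".

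**The concern.** The outcome definition gives one time and one source, and both are the 1-week visit. Two earlier records of the same kind of event exist and are not mentioned. Several listed events can start and stop inside the first week, so a headache noted at the 24 h call and gone by day 3 enters the outcome only if it is asked about and recalled on day 7. A temperature taken at the 1-week visit says nothing about day 2.

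Side effects are a stated secondary objective, and the Discussion gives the purpose of measuring them as learning which risks need more study and should be explained to patients. Table 1 already describes PRF as having shown no side effects so far. An outcome that can miss early events is a weak test of that statement. Incomplete capture lowers the reported percentage in each arm. If capture is equal in the two arms, it also shrinks the absolute difference between them.

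**Working it through.** **Which visit is the first visit.** The contacts in Duration of treatment and follow-up run: recovery at 30 min, phone call at 24 h, then visits at 1 week, 4 weeks, 2 months and 3 months. The first contact after discharge that is a visit is the one at 1 week. The two phrases in item 2 (the time and the recording point) therefore agree with each other, and both point to that visit.

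**What the definition leaves open.** It does not say whether the visit records everything since the procedure or only what is present that day. It neither includes nor excludes the recovery and 24 h records.

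**What the event list implies.** Two of six entries carry the label transient. To call an event transient, one needs a time at which it was present and a later time at which it was gone. The 24 h and 1-week contacts supply that pair, whereas status on day 7 alone does not. Dysesthesia appears on the short-term list and again on the persisting list, and the persisting list is also assessed at 1 week. Dysesthesia seen on day 7 therefore falls under both definitions, and the earlier records are what would help to separate them.

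**Size.** The article states no incidence, duration or recall figure, so there is nothing to reproduce. Everything below is an assumption, with 32 patients at 1:1 taken as 16 per arm.

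*General form.* Reported rate = p × s, where p is the true first-week incidence and s is the share of affected patients captured at the 1-week visit. With p = 20%, 16 × 0.20 = 3.2 affected patients per arm:

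| s | Captured patients per arm | Reported rate |
|---|---|---|
| 0.25 | 0.8 | 5% |
| 0.50 | 1.6 | 10% |
| 0.75 | 2.4 | 15% |
| 1.00 | 3.2 | 20% |

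Over p = 10% to 40% and the same values of s, the reported rate runs from 0.10 × 0.25 = 2.5% to 0.40 × 1.00 = 40%. If s is the same in both arms, the difference is multiplied by s and the ratio of rates is unchanged.

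*Worst case: status on day 7 only.* Take onset at the procedure and an exponential duration with median m days. The share still present is 0.5^(7/m) on day 7 and 0.5^(1/m) at 24 h. With p = 30%, 16 × 0.30 = 4.8 affected patients per arm. The number seen on day 7 is 4.8 × 0.5^(7/m), and the chance that an arm shows no event is (1 − 0.3 × 0.5^(7/m))^16.

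| m (days) | Present at 24 h | Present on day 7 | Seen on day 7, of 4.8 | Chance of no event in an arm |
|---|---|---|---|---|
| 1 | 50% | 0.8% | 0.04 | 0.96 |
| 2 | 71% | 9% | 0.42 | 0.65 |
| 3 | 79% | 20% | 0.95 | 0.37 |

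The onset assumption matters little. If every event began at 24 h instead, the day-7 share would be 0.5^(6/m), that is 1.6%, 12.5% and 25%.

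**Time windows for the same outcome.** Short-term is 4 weeks in the research question and 1 week in item 2. Long-term is beyond 3 months in the research question and beyond 1 week in item 2. Item 2 also assesses persisting effects at 6 weeks, a visit the schedule does not contain. Follow-up ends at 3 months, so nothing beyond 3 months can be observed.

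**The case against.** The strongest reply is that the list heading sets a window (the first week) and then says where it is written down. On that reading the visit collects all events since the procedure, a resolved event still counts, and labelling an event transient presupposes that a history is taken. Nothing in item 2 says that the earlier records are discarded or that fever is judged only by the temperature on day 7. How contacts are pooled is also the kind of detail that a condensed article may leave to the full protocol or the analysis plan.

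Much of this stands. A reader might infer that the outcome as written necessarily undercounts, that its events are mostly transient, or that PRF will come out looking almost free of side effects. The article supports none of these. The cumulative reading is open, and under it with full recall the loss is zero. Only two of six events are labelled transient, and no durations are given. Persisting effects have a measure of their own. The day-7 status figures do not apply under the cumulative reading.

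What does not stand is the appeal to omitted detail. The article does not leave the time and source unstated: it names one of each. Anyone following it would build the outcome from the 1-week record, and even on the favourable reading would rely on seven-day recall for events that may already have been written down at 24 h.

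**Conclusion.** The point holds in conditional form. Item 2 ties a first-week outcome to one recording point and does not use two records of the same events that the trial already takes, so early side effects can be undercounted. The loss could be severe if the outcome means status on day 7: between 80% and 99% of events under the assumed median durations of 1 to 3 days. It is only recall loss if the visit asks about the whole week, and nil if recall is complete. The article does not settle which reading applies and gives no rates, so no size can be claimed for this trial. With about 16 patients per arm, one patient moves an arm's percentage by about 6 points (1/16), so losing two or three patients' events would change the reported result visibly. This is a secondary outcome of a feasibility pilot. The definition should be corrected, but the defect does not threaten the primary feasibility aims.

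**What to change.** Rewrite the short-term part of item 2 along these lines:

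- The outcome is the percentage of patients with any listed event recorded at any contact from the end of the procedure to the 1-week visit. The contacts are the recovery check, the 24 h call, and the 1-week visit including the interval since the call.
- Each patient is counted once, and events are tabulated by arm and by contact. The tabulation keeps events seen only in recovery visible as such.
- Fever counts if reported or measured at any of these contacts.

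In the same edit, reconcile the windows for short-term and persisting effects with Secondary research questions, item 2, and with the visits in Duration of treatment and follow-up. Otherwise the outcome stays contradictory after the change.

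The cost is wording and one more table. No new contact is needed, and the reported percentage will be somewhat higher in both arms. One limit should be stated in the report. Trial status gives 28 of 32 interventions as complete, so patients already past week 1 cannot be asked the interval question afresh. Their 1-week record has to be used as it was taken, alongside their recovery and 24 h records. The definition should be fixed before the treatment codes are opened.
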